### Induced pluripotent stem cells, leukocytes and other blood cells

Leucocytes, preadipocytes, myoblasts and fibroblasts can be used for the production of induced pluripotent stem cells. Leukocytes and red blood cells are also extracted and stored live for future analyses, and extraction of DNA and RNA.

### Genetic, epigenetic, transcriptomic analyses and other omics analyses

DNA is isolated from a whole blood sample, tissue samples, feces and saliva. Genetic studies including genome-wide scans and sequencing technologies are performed to combine information obtained from genome-wide transcriptomics analyses of target tissues (adipose, skin, muscle, liver, gut, and so forth). Additionally, we will measure the mitochondrial DNA copy number of the tissues as an estimate of the mitochondrial amount. RNA isolated from blood, adipose tissue, muscle, skin or their cultures is used to study global tissue-specific RNA profiles. Epigenetic profiling of the tissues may include whole genome-scale methylation techniques.

Blood samples, tissue biopsies and urine samples are used for other omics analyses such as metabolomics, lipidomics and proteomics analyses. Saliva and fecal samples are used for microbiota analyses.

### Continuous glucose monitoring

CGM is carried out with the Freestyle Libre system (Abbott). The sensor is applied on the back of the upper arm and worn for 14 days per time point, during which all patients keep a food diary for 3 days.

### Hepatobiliary scintigraphy

Bile reflux is investigated with hepatobiliary scintigraphy as described elsewhere [15]. Scintigraphy is performed for all patient in the OAGB group of the HUH (40 patients) 6 months after the operation.

### Endoscopic and histological assessment

All patients undergo a gastroscopy with biopsies from the duodenum, antrum, corpus and gastroesophageal junction as a part of preoperative assessment. During the follow-up all OAGB patients at HUH are invited for a gastroscopy 6 months after OAGB to assess endoscopic signs of reflux. Gastroscopies are performed without sedation with a flexible endoscope (Olympus Q190, Tokyo, Japan). Mucosal biopsies are obtained from the jejunum, anastomosis, gastric pouch in 2-cm intervals, cardia and esophagus. Biopsy specimen are prepared with serial sections (5 μm thick) from formalin-fixed and paraffin-embedded biopsy specimen after hematoxylin and eosin and Alcian blue/periodic acid–Schiff staining.

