## Materials and methods

### Aims of the study

The primary outcome is weight loss 2 years after the operation. Weight loss is measured as percentage excess weight loss (%EWL) and percentage total weight loss (%TWL). %EWL is calculated as a percentage of lost excess weight since the preoperative visit compared to an ideal weight with a body mass index (BMI) of 25 kg/m^2^. Weight loss will also be analyzed as a grouping variable according to different categories of weight loss to compare responders and nonresponders to bariatric surgery. For EWL% we use the categories 0–24.99%, 25–49.99%, 50–74.99% and ≥75%, and for TWL% we use the categories <10%, 10–19.99%, 20–29.99%, 30–39.99%, ≥40% to determine participants with different amounts of weight loss achieved.

The secondary outcomes to be measured at the time points of 6 months, 12 months, 24 months, 5 years and 10 years are as follows:
Weight loss (%EWL, %TWL)Complications (any complication requiring any intervention or a prolonged hospital stay or additional outpatient visits)Perioperative factors (operation time, hospital stay, nausea, ability to take fluids and mobilization)Remission of comorbidities (including, for example, T2DM, hypertension, nonalcoholic fatty liver disease); remission is defined as normalization of measured values without medicationChanges in nutritional, metabolic and safety laboratory parameters (e.g., hemoglobin, vitamins, albumin, electrolytes, liver enzymes, lipids)Glucose tolerance and insulin response during an oral glucose tolerance test (OGTT) or meal testContinuous glucose monitoring (CGM)Changes in body composition (whole body fat with dual-energy x-ray absorptiometry (DEXA) and bioelectrical impedance (BIA), lean mass (DEXA and BIA), bone mineral mass and density (DEXA), subcutaneous fat (magnetic resonance imaging (MRI)), intra-abdominal fat (MRI), liver fat (magnetic resonance spectroscopy (MRS))Bile reflux at 6 months (for the OAGB group at Helsinki University Hospital (HUH))Tendency for urolithiasisChanges in cortisol and other hormone metabolismChanges in blood and tissue (adipose tissue, muscle) transcriptomics, proteomics, metabolomicsChanges in tissue (adipose tissue, muscle) mitochondrial activitiesChanges in gut and saliva microbiota and bile acid metabolismChanges in quality of life and lifestyle and gastrointestinal symptoms

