### Study sites and randomization

The trial is being carried out in two academic centers: HUH in collaboration with the University of Helsinki, and Oulu University Hospital (OUH). Both bariatric centers (HUH and OUH) are university hospitals that are tertiary referral bariatric centers with a catchment area of around one million people in Finland. Metabolic studies for patients in HUH are conducted by the Research Program for Clinical and Molecular Metabolism, University of Helsinki.

The trial is carried out according to the Consolidated Standards of Reporting Trials (CONSORT) statement. The trial schedule is shown in Fig. 1. Surgeons performing the intervention recruit eligible patients at a preoperative visit (study baseline) and randomize them according to protocol. This is an open-label study and the patients and surgeons are informed of the randomization outcome. Outcome analyses are also performed without blinding. Randomization is carried out as follows: 120 sheets of paper stating either “Single Anastomosis Gastric Bypass” or “Roux-en-Y Gastric Bypass” are divided into groups of four and six containing equal numbers of both outcomes and then sealed into opaque envelopes. These groups of opaque envelopes are distributed to both centers (80 envelopes for HUH and 40 envelopes for OUH) and then divided into two batches (for patients with diabetes and those without). The goal of this allocation sequence is to have equal numbers of patients in both groups at both centers and also an equal number of patients with diabetes in both groups at both centers.

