### Preoperative work-up and outpatient follow-up

#### Helsinki University Hospital and Oulu University Hospital

At 8 weeks prior to the operation (the baseline of the study), all patients are evaluated for eligibility for surgical treatment according to the Finnish guidelines for management of obesity and local protocols by an endocrinologist, surgeon, dietitian and anesthesiologist. This includes a thorough medical check-up with laboratory tests, BIA, assessment of obstructive sleep apnea and a gastroscopy. If the inclusion criteria are met and no exclusion criteria are found, patients can be recruited to this study. Written consent is received for all study patients. Together with extensive blood tests, we perform an OGTT to identify patients with impaired glucose tolerance or T2DM. Preoperatively, all patients also fill in questionnaires to assess diseases, medications, lifestyle and quality of life.

At 1 month after the operation, postoperative recovery and comorbidities are assessed together with blood tests and BIA.

At 3 months all patients meet with an internist or endocrinologist, and nutritional, metabolic and safety laboratory tests are evaluated and medications for comorbidities are reviewed and optimized (at HUH). At OUH, laboratory tests are analyzed, and patients are contacted via telephone.

At 6 months a gastroscopy with comprehensive biopsies of the gastric tube, gastroesophageal junction and esophagus as well as a radioisotope scanning for the detection of bile reflux are performed (for the OAGB group at HUH).

At 6 months,12 months, 24 months, 5 years and 10 years BIA measurement and OGTT are repeated according to the same protocol as prior to the operation. Accordingly, nutritional, metabolic and safety laboratory tests are again performed. All patients also fill in questionnaires and food diaries (at HUH). At OUH, all patients meet an endocrinologist, and nutritional, metabolic and safety laboratory tests are evaluated and medications for comorbidities are reviewed and optimized.

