### Statistical analyses

Normally distributed variables will be expressed as the mean and SD, and non-normally distributed variables will be expressed as the median and interquartile range; categorical variables will be expressed as the number and percentage.

To test the group differences (OAGB vs RYGB) in the primary and secondary endpoints, we will use the Student’s *t* test for continuous normally distributed variables, the Mann–Whitney *U* test for continuous non-normally distributed data, and the chi-squared test or Fisher’s exact test for categorical variables. Additionally, we will conduct multivariable analysis with generalized mixed linear regression or logistic regression models with adjustment for possible confounding factors. The statistical analyses will be conducted on an intention-to-treat basis. A *P* value < 0.05 will be considered statistically significant.

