## Conclusion

Obesity is a multifactorial disease and treatment needs to be aimed at all aspects of the metabolic syndrome. Ever since the early days of bariatric surgery there has been enormous interest in finding out which is the optimal procedure. Each operation has its pros and cons and the definition of what is optimal is not clear. First, we need to discover the true underlying mechanisms of surgery-induced weight loss and remission of comorbidities and which of these mechanisms are related to a specific surgery and not just weight loss per se. Many studies have shown the metabolic effects of bariatric surgery and nowadays it is more appropriate to talk about metabolic surgery. The comparison of RYGB with OAGB has for a long time been a matter of opinion since there have not been enough data from randomized controlled trials, and both techniques have shown great results [9].

Our current study takes on a comprehensive approach to the entire concept of metabolic surgery and weight loss.

First, we are comparing RYGB and OAGB in a randomized controlled setting to find out whether there is a difference in weight loss, postoperative symptoms, adverse effects, comorbidity remission and quality of life between the procedures. We intend that any small differences between these techniques will help us understand which patient would benefit from a certain technique. Our study protocol includes a thorough follow-up with regular outpatient visits including blood analyses, body composition measurements and questionnaires. Bile reflux is measured with a specific scintigraphic method which we have previously tested in a pilot series [15]. In the current study, the scan is prolonged to 90 min to view the entire potential bile exposure of the gastric tube and esophagus. The risk of urolithiasis is analyzed from diurnal urine samples, blood analyses and DEXA measurements.

Second, we want to discover the metabolic effects of surgery and weight loss at a cellular level by measuring changes in mitochondrial activity and the interplay between gut hormones, bile acids, gut microbiota and the regulation of glucose homeostasis. We use novel analytic mechanisms for measuring energy expenditure and mitochondrial activity. Gut hormone and bile acid responses to meal stimulation are measured and glucose homeostasis is studied with CGM and repeated OGTT during the follow-up.

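### Only OAGB patients at Helsinki have a scheduled 6-month gastroscopy and scintigraphy, so the between-arm comparison of later complications is open to detection bias

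*Protocol article*

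**What the plan says.** **Who is examined.** The section Endoscopic and histological assessment states: "During the follow-up all OAGB patients at HUH are invited for a gastroscopy 6 months after OAGB to assess endoscopic signs of reflux". Biopsies are taken at that examination. The Hepatobiliary scintigraphy section states: "Scintigraphy is performed for all patient in the OAGB group of the HUH (40 patients) 6 months after the operation". The follow-up schedule for the two hospitals repeats the limit: "a radioisotope scanning for the detection of bile reflux are performed (for the OAGB group at HUH". The Abstract agrees for bile reflux testing. The article describes no scheduled postoperative gastroscopy or scintigraphy for RYGB patients or for anyone at Oulu. Only the preoperative gastroscopy is common to all patients.

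**What counts as a complication.** Aims of the study lists as a secondary outcome "Complications (any complication requiring any intervention or a prolonged hospital stay or additional outpatient visits". The article gives no rule for findings that come to light only through the OAGB-only examination.

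**What is compared.** The Statistical analyses section lists its tests with the purpose "To test the group differences (OAGB vs RYGB) in the primary and secondary endpoints" and names no exception. Among the secondary outcomes, Aims of the study includes "Bile reflux at 6 months (for the OAGB group at Helsinki University Hospital (HUH".

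**Blinding.** Study sites and randomization says that the trial is open label and that outcomes are analysed unblinded.

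**The concern.** A fair comparison of complication rates needs the arms to be searched with equal intensity. Here most OAGB patients are actively examined at 6 months and no RYGB patient is. Suppose the examination shows something that causes no symptoms, and it is then treated or followed up at an extra visit. After OAGB it meets the definition of a complication. The same silent finding after RYGB would not be looked for.

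The Conclusion of the article names adverse effects among the things to be compared first, and the Introduction cites the claim that OAGB is less prone to complications. A difference in detection could be reported as a difference in safety, or could mask a true advantage of OAGB. Open-label conduct and unblinded analysis offer no protection.

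There is also a wording mismatch. The general sentence on testing covers all secondary endpoints, but bile reflux is measured in one arm only.

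**Working it through.** **1. The plan's own count.** Study sites and randomization gives "80 envelopes for HUH and 40 envelopes for OUH" with equal allocation. OAGB at Helsinki is 80 / 2 = 40, which matches the 40 patients in the scintigraphy section. Sample size gives 60 per arm. Share with a scheduled examination: OAGB 40/60 = 67%, RYGB 0/60 = 0%. Patients are invited to the gastroscopy, so 40 is an upper limit.

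**2. Which findings can tilt the count.** Three conditions must all hold: the finding is silent, it is first made at the OAGB-only examination, and it leads to treatment or an additional visit. The scheduled examination itself does not count, nor does a finding with no consequence. Events before the 6-month examination are unaffected.

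**3. Possible size, in counts.** The documents give no yield. Assume that 5% to 20% of the 40 gain a countable event.
- Extra events: 40 × 0.05 = 2 to 40 × 0.20 = 8.
- On 60 patients: 2/60 = 3.3 to 8/60 = 13.3 percentage points.

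With an assumed 6/60 in both arms before these are added (Fisher's exact test, two-sided):

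| Extra OAGB events | RYGB vs OAGB | P |
|---|---|---|
| 2 | 6/60 vs 8/60 | 0.78 |
| 4 | 6/60 vs 10/60 | 0.42 |
| 6 | 6/60 vs 12/60 | 0.20 |
| 8 | 6/60 vs 14/60 | 0.085 |

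**4. Possible size, as a false-positive risk.** Let c be the rate of clinically presenting complications, equal in both arms. Let q be the share of examined OAGB patients without such an event who gain one through the examination. The apparent OAGB rate is c + (40/60)(1 − c)q. For c = 10% and q = 5% this is 0.10 + 0.667 × 0.90 × 0.05 = 0.13. The last column is the chance that an uncorrected chi-squared test at two-sided 0.05 shows a significant OAGB excess, summed over the binomial distributions.

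| q (c = 10%) | Apparent OAGB rate | Chance of a false OAGB excess |
|---|---|---|
| 0 | 10% | 2.5% |
| 5% | 13% | 7% |
| 10% | 16% | 15% |
| 20% | 22% | 43% |

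At q = 10% the chance is about 24% for c = 5% and about 10% for c = 20%.

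**5. The offset.** Interim results counts an additional gastroscopy for eating difficulties as a Clavien–Dindo IIIa event, even where the finding was normal. A scheduled gastroscopy could replace such a symptom-driven one. If a share s of events in the 40 were absorbed this way, the OAGB rate would be c(1 − (40/60)s). With c = 10%, s = 25% gives 8.3% and s = 50% gives 6.7%. The latter loss of 3.3 points is about as large as the 3-point gain at q = 5%.

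**6. After the fix.** If events found only at the OAGB-only examination leave the comparison and symptomatic ones stay, q and s no longer act on one arm. The chance of a false OAGB excess is then about 2.3% to 2.5% for c from 5% to 20%.

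**The case against.** The examination is deliberate: the Introduction raises bile reflux as a concern specific to OAGB. The complication definition asks for an intervention, a longer stay or additional visits, so many silent findings would never qualify. Complications are one of many secondary outcomes. The primary outcome, weight loss, is not touched, and neither are perioperative and early events. Interim results shows that the reason for an extra gastroscopy is noted, and a full protocol or case-report form may hold attribution rules. All of this stands, and it limits the importance of the point. It does not make ascertainment equal, because the definition and the comparison are both stated in the text and neither sets screen-detected findings apart.

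Three stronger readings are tempting, and the documents do not support them:
- **That the complication comparison is shown to be tilted by a known amount.** The yield and the base rate are both assumed. Even the top of the assumed range in the count table gives P = 0.085, and the offset could cancel a small tilt.
- **That the plan commits to an impossible reflux test.** Aims of the study openly restricts bile reflux to OAGB at Helsinki. The testing sentence is general and does not name it. What remains is a wording mismatch.
- **That the lengthened scan is a fault.** The Conclusion discloses it ("In the current study, the scan is prolonged to 90 min to view the entire potential bile exposure"), and no comparison with the pilot series is planned.

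**Conclusion.** The point holds as a risk of detection bias in one secondary comparison. Up to 40 of 60 OAGB patients and 0 of 60 RYGB patients have the scheduled examination, and the complication definition can take in what it finds. The expected direction is against OAGB, for complications from 6 months on.

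The size is unknown. Under an assumed yield of 5% to 20%, the distortion is 3 to 13 percentage points before any offset. It is zero if no silent finding leads to treatment or a visit. The conclusion assumes that no rule elsewhere in the full protocol already separates screen-detected events. The bile reflux issue needs only a clarifying sentence. The matter is worth correcting because the correction is cheap; it does not threaten the trial's main result.

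**What to change.** 1. Record for each complication how it was detected: by symptoms, at a visit or test scheduled in both arms, or only at the OAGB-only 6-month examination.
2. Compare the arms on events that were symptomatic or were found at a visit or test scheduled in both arms. Keep a symptomatic event even if its cause was identified at the OAGB-only examination; otherwise the bias would turn in favour of OAGB.
3. Report the all-events comparison alongside, and list screen-detected OAGB findings separately.
4. State in the Statistical analyses section that bile reflux is reported as a single-arm proportion with an exact 95% confidence interval for OAGB at Helsinki, outside the between-group tests.

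The cost is one field on the case-report form, some endpoint wording and one additional analysis. No new procedure is needed and the sample size is unaffected. The downside is that one of the two comparisons omits asymptomatic screen-detected OAGB events. The all-events analysis restores them.

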### Questionnaires and food diaries

All patients fill out questionnaires that extensively survey their quality of life, physical activity, social activity, gastrointestinal symptoms, eating behavior, sleep, mental state and general health status. A food diary is additionally kept for 3 days to measure nutritional intake for patients operated on at HUH.

### Ethical approval and informed consent

All procedures performed in studies involving human participants are in accordance with the ethical standards of the Institutional Research Committee and with the 1964 Helsinki Declaration and its later amendments or comparable ethical standards. The trial has been reviewed by Helsinki University Hospital ethics committee (HUS/1706/2016) and approved by the Helsinki University Hospital Research Review Board (HUS269/2017). The trial is registered at www.clinicaltrials.gov (NCT02882685. Informed consent was obtained from all individual participants.

### Statistical analyses

Normally distributed variables will be expressed as the mean and SD, and non-normally distributed variables will be expressed as the median and interquartile range; categorical variables will be expressed as the number and percentage.

To test the group differences (OAGB vs RYGB) in the primary and secondary endpoints, we will use the Student’s *t* test for continuous normally distributed variables, the Mann–Whitney *U* test for continuous non-normally distributed data, and the chi-squared test or Fisher’s exact test for categorical variables. Additionally, we will conduct multivariable analysis with generalized mixed linear regression or logistic regression models with adjustment for possible confounding factors. The statistical analyses will be conducted on an intention-to-treat basis. A *P* value < 0.05 will be considered statistically significant.

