### Sample size

This study is designed as a superiority trial based on previous cohort series. According to power calculations finding a difference of 10 in %EWL with the assumptions of mean %EWL = 60 (standard deviation (SD) = 17) in the RYGB group, with alpha = 0.05, 50 patients in each group would be sufficient to reach the power of 80%. If a drop-out of 10% is taken into account, this would mean 55 patients per group. Power calculations were performed by simulation using the Mann-Whitney-Wilcoxon test (PASS v13.0, NCSS Inc., Kaysville, Utah, USA). Since there was a lack of published data on comparisons between these two operations at the time of designing the study, we decided to recruit 60 patients for both treatment groups in order to have sufficient statistical power regarding the primary end point (10% difference in %EWL at 2 years between the groups).

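### Secondary outcomes worded as changes get an unadjusted two-sample test as the group comparison; a test adjusted for the outcome's own baseline would be more precise at no cost

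*Protocol article*

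**What the plan says.** Under Aims of the study, the protocol article lists secondary outcomes at 6, 12 and 24 months and at 5 and 10 years. Several are worded as changes: laboratory values, body composition ("Changes in body composition"), hormone metabolism, omics, mitochondrial activity, microbiota and bile acids, and quality of life. Others are not, such as complications, perioperative factors, remission and bile reflux.

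Under Statistical analyses, one rule covers all endpoints. "To test the group differences (OAGB vs RYGB) in the primary and secondary endpoints", the t test is used for normally distributed variables, the Mann-Whitney test for other continuous variables, and chi-squared or Fisher tests for categorical ones. None of these takes a covariate. The section then continues: "Additionally, we will conduct multivariable analysis with generalized mixed linear regression or logistic regression models", "with adjustment for possible confounding factors". The factors are not named, the outcome's own baseline is not mentioned, and the adjusted model is not given precedence.

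**The concern.** Read together, the two sections most naturally mean that the change from baseline is compared between arms by an unadjusted test. A change score contains the baseline value with a negative sign, so baseline variability that could be removed stays in the test. Adjusting for baseline removes it.

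The additional model does not settle this. In a randomised trial the reason to adjust for an outcome's baseline is precision, and a criterion of possible confounding need not select it.

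What is at stake is sensitivity for secondary outcomes. Blood tests, bioelectrical impedance and questionnaires cover both centres, but the extensive metabolic work rests on the 80 Helsinki patients, about 40 per arm. The article's Conclusion hopes to learn from small differences between the techniques and concedes that some secondary outcomes may be underpowered.

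**Working it through.** **The plan's own figure.** The article gives a power figure only for the primary outcome, based on "finding a difference of 10 in %EWL with the assumptions of mean %EWL = 60 (standard deviation (SD) = 17) in the RYGB group". It puts the need at 50 per arm for 80% power at the 5% level. With two-sided alpha 0.05 (assumed, since sidedness is not stated), the t test needs 2 × (1.960 + 0.842)² × 17² / 10² = 45.4, so 46 per group. Dividing 46 by the Mann-Whitney relative efficiency of 0.955 gives 48.2, so 49. A simulation of the Mann-Whitney test on normal data with 50 per group gives 80.8% power. The stated 50 is therefore reproduced. No figure is stated for any change outcome.

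**Inputs for the change outcomes.** The correlation r between baseline and follow-up and the ratio k of follow-up SD to baseline SD are not in the documents. Both are assumed here: r = 0.3, 0.5 and 0.7, with k = 1 (spread unchanged) and k = 0.7 (spread narrowed by surgery).

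**Formulas**, with baseline SD = 1, a linear relation and a common slope in both arms:
- Variance of the change: 1 + k² − 2rk
- Variance after ANCOVA: k²(1 − r²)
- Variance of the follow-up value alone: k², so its ratio to ANCOVA is 1/(1 − r²) whatever k is
- Power of the unadjusted test where ANCOVA has 80%: Φ(2.802/√ratio − 1.960), a normal approximation that ignores ANCOVA's one extra degree of freedom and does not depend on the number of patients

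**Example.** At r = 0.5 and k = 1, the change has variance 1 + 1 − 1 = 1 and ANCOVA 0.75. The ratio is 1.33 and the power Φ(2.802/1.155 − 1.960) = Φ(0.466) = 68%.

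**Variance ratio to ANCOVA, and power where ANCOVA has 80%:**

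| r | Change, k = 1 | Change, k = 0.7 | Follow-up value alone |
|---|---|---|---|
| 0.3 | 1.54, 62% | 2.40, 44% | 1.10, 76% |
| 0.5 | 1.33, 68% | 2.15, 48% | 1.33, 68% |
| 0.7 | 1.18, 73% | 2.04, 50% | 1.96, 52% |

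The ratio is also the factor by which the unadjusted test would need more patients. With equal SDs and higher correlation the loss on change is small: 76% power at r = 0.8 and 78% at r = 0.9.

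**In terms of detectable difference.** With 40 per arm, r = 0.5 and k = 1, the difference found with 80% power is 2.802 × √0.75 × √(2/40) = 0.54 SD by ANCOVA and 2.802 × 1 × √(2/40) = 0.63 SD by the test on change.

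**Validity of the test on change.** A simulation of 40,000 trials with 54 per arm (60 less 10%) and equal SDs gives type I error of 4.8% to 5.2% for r from 0.3 to 0.8, with mean bias of zero. Given a chance baseline difference, the estimate moves by −(1 − r) times that difference, for example −0.50 at r = 0.5. Among trials where the imbalance exceeds one standard error, the error rate is 10.2%, 9.0% and 7.5% at r = 0.3, 0.5 and 0.7.

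**The case against.** Four objections deserve an answer.

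- **The tested quantity is inferred.** The Statistical analyses section never says that the change enters the test, and outcomes measured at fixed visits could equally be compared on follow-up values. This stands. It alters the size of the loss, but not the remedy: the last column of the table shows that ANCOVA is still more precise.
- **An adjusted model is already planned.** It belongs to the right family, and a full covariate list is properly left to an analysis plan that is not shown. This also stands. What the article does state is the order: unadjusted tests make the comparison and the model is additional. That choice can be improved.
- **The large losses rest on assumptions.** A reader might infer that these tests lose much of their power as a matter of fact. The documents support no such statement, since they give neither r nor any narrowing of the spread. Narrowing is plausible for a variable such as liver fat, but that cannot be carried over to every laboratory, tissue or quality-of-life measure. The power figures also apply to normal data and the t test; none was computed for the Mann-Whitney test.
- **The comparison is randomised.** A reader might infer that a test on change compares which arm started worse. It does not do so on average, because it is unbiased and keeps its error rate. Only a chance imbalance in the particular sample shifts the result. Separate allocation by centre and diabetes limits such imbalance only in part.

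The cellular aim in the Conclusion, "measuring changes in mitochondrial activity", is partly a within-patient question for which change is the natural quantity. The point here is confined to the OAGB versus RYGB comparison.

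**Conclusion.** The point holds as one of efficiency, not validity. For continuous secondary outcomes worded as changes, the stated group comparison leaves out the outcome's own baseline, and adjusting for it gives a more precise test on either reading of the plan. For a test on change with equal SDs and r of 0.3 to 0.7, the cost is about 7 to 18 power points from 80%. It is about 30 to 36 points if the follow-up SD is 70% of baseline. For a test on follow-up values, the cost over the same range of r is about 4 to 28 points. All these sizes depend on r, and those for change also on k; neither is in the documents. The primary outcome, its sample size and the categorical outcomes are not touched.

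**What to change.** In the Statistical analyses section, state that for each continuous secondary outcome worded as a change, the main OAGB versus RYGB test is an ANCOVA, or the mixed model already planned, of the follow-up value on arm and the same variable's baseline, transformed if skewed. Report mean or median change descriptively, and keep the t or Mann-Whitney test as a sensitivity analysis.

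The cost is wording. The baseline measurements are already scheduled in the preoperative work-up and at the Obesity Research Unit, so no patient, visit or sample is added.

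### A supplementary analysis sorts weight loss into ordered classes, but the stated test for categorical variables ignores order: about 62% power against about 78% if the arms are compared on the %EWL classes

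*Protocol article*

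**What the plan says.** All references are to the protocol article.

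- **Aims of the study.** The primary outcome is weight loss 2 years after surgery, expressed as %EWL and %TWL, both continuous. The same paragraph adds: "Weight loss will also be analyzed as a grouping variable according to different categories of weight loss to compare responders and nonresponders to bariatric surgery". The %EWL classes are cut at 25, 50 and 75 (four classes) and the %TWL classes at 10, 20, 30 and 40 (five classes).
- **Statistical analyses.** The tests for OAGB versus RYGB on primary and secondary endpoints are fixed by type of variable. Continuous variables get the t test if normal and Mann-Whitney if not. The rest get "the chi-squared test or Fisher’s exact test for categorical variables". Mixed linear or logistic regression is additional. No ordinal model or trend test is named.
- **Sample size.** The target is "finding a difference of 10 in %EWL with the assumptions of mean %EWL = 60 (standard deviation (SD) = 17) in the RYGB group", and "Power calculations were performed by simulation using the Mann-Whitney-Wilcoxon test". This gives 50 per group for 80% power. Then: "If a drop-out of 10% is taken into account, this would mean 55 patients per group". The trial finally chose 60 per group.

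**The concern.** The classes are ordered, and the trial is sized for a shift in one direction. A chi-squared or Fisher test on four classes treats them as interchangeable labels. It spends three degrees of freedom on a contrast that an ordered test addresses with one.

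If the assumed 10-point difference is real and the arms are compared on class, the class table could well come out non-significant beside a significant continuous result in the same patients. It might then be read as showing that the operations do not differ in level of response. The Conclusion says the investigators hope small differences will help match technique to patient, so results by response level are likely to be interpreted.

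This is not a detail left to an unseen analysis plan. The article states a rule by variable type, and that rule suits ordered classes badly.

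**Working it through.** **Inputs.** From Sample size: difference 10, RYGB mean 60, SD 17, alpha 0.05, 50 per group before drop-out, 10% drop-out, 60 per group recruited. From Aims of the study: cuts at 25, 50 and 75. Assumed, because not stated: normal data, the same SD in both arms, a two-sided test. Evaluable number: 60 × 0.9 = 54 per arm.

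**Step 1: the plan's own figure.** For a comparison of means, n = 2 × (1.96 + 0.8416)² × (17/10)² = 2 × 7.849 × 2.89 = 45.4, so 46 per group. Dividing by the Mann-Whitney efficiency of 0.955 gives 48.2. Simulated Mann-Whitney power at 50 per group is about 81%. The stated 50 per group is reproduced. For drop-out, 50 × 1.1 = 55, as stated.

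**Step 2: class shares under those assumptions.**

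| Mean %EWL | <25 | 25 to <50 | 50 to <75 | ≥75 |
|---|---|---|---|---|
| 60 | 0.020 | 0.258 | 0.533 | 0.189 |
| 70 | 0.004 | 0.116 | 0.496 | 0.384 |
| 50 | 0.071 | 0.429 | 0.429 | 0.071 |

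**Step 3: chi-squared on the four classes.** The noncentrality is n × Σ(p − q)²/(p + q), with 3 degrees of freedom.
- 60 versus 70: 54 × (0.0103 + 0.0545 + 0.0013 + 0.0667) = 54 × 0.1329 = 7.18; power 60%.
- 60 versus 50: 54 × 0.1361 = 7.35; power 61%.

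Simulation (20,000 trials, empty classes dropped) gives 62% and 61%.

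**Step 4: an ordered test on the same classes.** As an approximation, score the classes 0 to 3.
- 60 versus 70: the mean scores are 1.891 and 2.261, a difference of 0.370. The variance is 0.515 pooled under the null, and 0.514 and 0.448 within arms. Then z = (0.370 − 1.96 × √(2 × 0.515/54)) / √((0.514 + 0.448)/54) = (0.370 − 0.271)/0.133 = 0.74, so power is 77%.
- 60 versus 50: the same steps give 78%.

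Simulation gives 77 to 78% for Mann-Whitney on the classes and 78 to 79% for the trend test.

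**Step 5: sensitivity to n (simulated; ranges cover both directions of effect).**

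| n per arm | Chi-squared, classes | Mann-Whitney, classes | Mann-Whitney, full scale | t test |
|---|---|---|---|---|
| 50 | 57–58% | 75% | 81–82% | 83% |
| 54 | 61–62% | 77–78% | 84% | 86% |
| 60 | 67% | 82–83% | 88% | 89% |

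The gap between the two tests on the same classes is about 15 to 18 points throughout.

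**Step 6: does switching to Fisher help?** The lowest class is sparse. At 54 per arm it expects 54 × 0.020 = 1.1 RYGB patients, against 54 × 0.004 = 0.2 OAGB patients if OAGB is better or 54 × 0.071 = 3.8 if it is worse. Nearly every simulated trial had an expected count below 5, so Fisher would often be the test used. The exact Fisher-Freeman-Halton test (3,000 trials) has 63 to 64% power at 54 per arm and 68 to 71% at 60. That is slightly better than chi-squared but still well short of the ordered test.

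**%TWL.** The documents give no mean or SD for %TWL. Converting by an assumed baseline BMI of 44 (%TWL about 0.43 × %EWL, SD 7.3) gives about 57% versus 79% at 54 per arm. The conversion uses a single BMI and ignores its spread, so these figures are illustrative only.

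**The case against.** The strongest objection is that the plan never expressly says the arms will be compared on class. The classes are a grouping variable for responders and nonresponders, which may mean comparing patients in one class with patients in another. The chi-squared or Fisher rule governs a different contrast, OAGB versus RYGB. This stands as a limit: the 62% applies if the arms are compared on the classes. It does not remove the point, because the only rule given for such a comparison is order-blind.

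A reader might infer that the classes are one form of the primary outcome, and so that the primary analysis loses power. The documents do not support that. The primary outcome is measured as continuous %EWL and %TWL, the classes are introduced with the word for an addition, and the sample size rests on the continuous scale.

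A reader might also infer that the classes replace continuous weight loss in the responder analyses. Nothing says so, and no test is named for them. Illustrative power losses of 15 to 25 points can be produced by assuming 72 patients, correlations of 0.25 to 0.40 and a one-way comparison of four classes, but none of these is a planned input.

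Finally, chi-squared on ordered classes is a valid test and can detect non-monotone differences. That is true, so the issue is efficiency and not error control. The absence of a cited source for prespecified cuts is no fault in a condensed article.

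**Conclusion.** The point holds as a minor one about a supplementary analysis. Read literally, the stated rule sends any between-arm comparison of the ordered classes to a test that ignores order. For %EWL at 54 per arm, a true 10-point difference would be missed more than one time in three (power about 62%), against a little over one in five with an ordered test (about 78%). This rests on the plan's means and SD, plus assumed normality, a common SD and a two-sided 5% level. It is conditional on the arms being compared on class. The powered continuous comparison, at 84 to 86%, is untouched. No firm size can be given for the %TWL classes or for the responder analyses.

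**What to change.** - **Statistical analyses:** limit the chi-squared and Fisher tests to binary or unordered variables. State that the ordered %EWL and %TWL classes, where compared between arms, will be tested with the tie-corrected Mann-Whitney test or a proportional-odds model. Mann-Whitney is already in the plan and only needs extending to ordered variables.
- **Aims of the study:** where the classes group patients in the responder analyses, also report the analysis with continuous %EWL or %TWL as the explanatory variable, with a curved term if the relation is not linear. Keep the class tables for description.

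The cost is about one sentence in each section, with no new data or patients. The downside is that an ordered test is less sensitive to a non-monotone difference, such as one arm having more patients in both extreme classes. The class table would still show that pattern.
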